### Relevant concomitant care permitted or prohibited during the trial {11d}

There is no specific concomitant care administered nor prohibited during the trial.

### Provisions for post-trial care {30}

There is no anticipated harm or compensation for trial participation.

### Outcomes {12}

#### Primary outcome measure

The primary outcome of this study will be the functional outcome assessed with the modified Rankin Scale (mRS), 90 days after the endovascular thrombectomy. To improve the follow-up rate, we defined 90 days as 90 ± 14 days after the endovascular thrombectomy to consider situations such as holidays. The mRS is a 7-grade categorical scale ranging from 0 (no symptoms) to 6 (death). Success will be considered as a mRS of 0–2 (functional independence). The mRS will be assessed by trained research staff blinded to the randomization group.

#### Secondary outcomes measures

The secondary outcomes of this study will be as follows:NIHSS score at day 1, day 2, and at the time of hospital discharge.mRS at the time of hospital discharge.Percentage of patients who cannot be extubated in the assigned group.Complications associated with mechanical ventilation: pulmonary injuries (barotrauma or volutrauma), respiratory infections (ventilator-associated pneumonia, bronchoaspiration), airway, oral or pharyngeal injuries, and others.Complications during ICU and hospital stay: intracranial hemorrhage, hemorrhagic transformation, reperfusion syndrome, need for craniectomy, prolonged mechanical ventilation in ICU (> 24 h), prolonged mechanical ventilation in ICU (> 48 h), reintubation, prolonged ICU stay (> 48 h), pneumonia, bronchoaspiration, other infection, in-ICU mortality, in-hospital mortality, and other complications.ICU and Hospital length of stay.Work-flow time, including stroke onset to door time, to artery puncture, and to reperfusion or procedure completion.

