#### Secondary objectives

The study will also investigate the effect of early (< 6 h) vs delayed (6–12 h) extubation after endovascular thrombectomy under general anesthesia for acute ischemic stroke, examining additional outcomes: the percentage of patients unable to be extubated in the assigned group, NIHSS scores on days 1 and 2, time to hospital discharge, mRS scores at hospital discharge, complications during ICU and hospital stay, and lengths of stay in the ICU and Hospital. We aim to identify factors that may influence poorer functional status at hospital discharge (NIHSS and mRS scores) and at 90 days (mRS score).

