## Data collection and management

### Plans for assessment and collection of outcomes {18a}, plans to promote participant retention and complete follow-up {18b}, data management {19}, confidentiality {27}

Pseudonymized data will be collected and managed in an electronic case report form (eCRF) specifically designed and validated for this purpose. Access to data will comply with local, national, and European Union data protection regulations. Each patient will be assigned a unique trial identification number, which will be disassociated from their personal information. The database will be protected by encryption software. Only the investigators and research team will have access to any protected health information of study participants and any study data. Any protocol deviations will be recorded on the eCRF, and a clinical research assistant will ensure that all protocol deviations and adverse events are recorded in the database. The following data will be registered:

Baseline characteristics and intraoperative data will include:Demographic data (age, height, weight, gender, and body mass index)American Society of Anesthesiologists physical statusSignificant comorbidities (cardiovascular, respiratory, neurological, cancer, atrial fibrillation, smoking, statin use, antiplatelet and anticoagulant treatments)NIHSS score at admissionTime of symptom onset, time of arrival at the hospital, time of first image for diagnosis, time of arterial puncture, time of tracheal intubation, time of recanalizationType of anesthesia (general anesthesia vs. sedation)Modified Thrombolysis in Cerebral Infarction (mTICI) scoreNeed for norepinephrine during endovascular treatmentIntraoperative complications (hypotension, hypertension, duration of procedure, stroke localization, intravenous fibrinolysis if applicable)Type of endovascular stroke treatment (direct aspiration, stent retriever, angioplasty, etc.)Procedural-related complications.

ICU data:Duration of mechanical ventilation (hours)pO2 at ICU admissionTime of extubationNeed for norepinephrine during mechanical ventilation and after mechanical ventilationMechanical ventilation complications (pneumothorax, pneumonia, etc.)Duration of ICU stay (hours)Complications during ICU stay (reintubation, infection, prolonged mechanical ventilation (> 48 h), prolonged ICU stay (> 48 h), ICU mortality, and other complications)

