#### Analysis of the secondary outcomes

The techniques that will be used to answer the secondary objectives will be fundamentally statistical inference techniques. The selection of each of them will depend on the nature of the variables involved, as well as their adjustment to normality.

All these analyses will be carried out with the statistical program SPSS 19.0 and those whose *p*-value is lower than 0.05 will be considered statistically significant values.

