### Methods in analysis to handle protocol non-adherence and any statistical methods to handle missing data {20c}

We will conduct analyses based on the intention-to-treat principle, meaning that participants are included in the final analysis regardless of adherence to the assigned treatment. As a sensitivity analysis, per-protocol analysis may be employed to complement the main analysis results. Missing data will be addressed through inverse probability weighting and worst-case imputation methods.

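### Length of stay and time to discharge are compared as plain durations that do not separate discharge alive from death, so more early deaths can make an arm's hospital stay look shorter

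*Protocol article*

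**What the plan says.** The protocol article's Secondary outcomes measures list "ICU and Hospital length of stay". Its Secondary objectives name "time to hospital discharge, mRS scores at hospital discharge, complications during ICU and hospital stay, and lengths of stay in the ICU and Hospital"; time to discharge appears there and not in the outcome list. The data collection section (items 18a to 27) records ICU stay as a duration in hours and hospital stay as a duration in days.

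For the comparison between arms, Analysis of the secondary outcomes names no test: "The selection of each of them will depend on the nature of the variables involved, as well as their adjustment to normality". Results with p below 0.05 count as significant. Item 20c sets the population, in which "participants are included in the final analysis regardless of adherence to the assigned treatment", and adds that "Missing data will be addressed through inverse probability weighting and worst-case imputation methods".

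Death appears in two other places. The complications outcome includes "in-ICU mortality, in-hospital mortality, and other complications", and the primary outcome gives death the worst grade, mRS 6.

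**The concern.** A recorded stay ends either because the patient left alive or because the patient died. These are opposite results, and a plain duration does not tell them apart. In an ordinary two-sample comparison of all randomised patients, a patient who dies on day 2 contributes 2 days and ranks ahead of a survivor discharged on day 8. The missing-data rule does not catch this, because the stay of a patient who died is observed, not missing.

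The article expects some deaths before discharge, since it lists in-ICU and in-hospital mortality as outcomes. Its Background describes hazards on both sides: pneumonia with longer ventilation, and aspiration and reintubation with premature extubation. Mortality could therefore differ between arms in either direction. At stake is a secondary result in which an excess of early deaths is reported as a shorter hospital stay.

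**Working it through.** **The plan's own figure.** None is given for length of stay. The arm size used below comes from Sample size {14}. With 55.5% versus 33.9%, two-sided 5% and 80% power, the mean proportion is 0.447, and

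n = [1.96·√(2·0.447·0.553) + 0.84·√(0.555·0.445 + 0.339·0.661)]² / 0.216² ≈ 82 per arm.

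Allowing for 5% losses, 82/0.95 = 86.3, so 87 per arm and 174 in total, as stated.

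**Assumed inputs (not in the article).** Survivors' hospital stay has the same gamma distribution in both arms (shape 3, mean 10 days). Time to death is exponential with a mean of 4 days. In-hospital mortality is 10% in one arm and higher in the other.

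**Effect on the mean.** If mortality is p, the mean recorded stay is (1 − p)·10 + p·4.

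- 10% deaths: 9.0 + 0.4 = 9.4 days
- 15% deaths: 8.5 + 0.6 = 9.1 days
- 20% deaths: 8.0 + 0.8 = 8.8 days
- 25% deaths: 7.5 + 1.0 = 8.5 days

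The gap between arms is (difference in p) × (mean time to death − mean survivor stay). At 20% versus 10% it is 0.10 × (4 − 10) = −0.6 days, with no difference among survivors.

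**Effect on the test.** Rank-sum test, two-sided p < 0.05, 87 per arm, by simulation. The table gives the share of trials in which the higher-mortality arm is significantly shorter. The second model uses lognormal stays, with a median of 9 days for survivors and 3 days for deaths.

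| Deaths | Gamma model | Lognormal model | Lognormal, deaths ranked longest |
|---|---|---|---|
| Equal | 2.4% | 2.6% | 2.1% |
| 15% v 10% | 5 to 6% | 6.0% | 0.8% |
| 20% v 10% | about 12% | 12.6% | 0.1% or less |
| 25% v 10% | about 20% | 24.0% | 0.1% or less |

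The equal row uses 15% in both arms for the gamma model and 10% in both for the lognormal model.

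**Sensitivity to timing.** If deaths come at a mean of 8 days, the gap at 20% versus 10% falls to 0.10 × (8 − 10) = −0.2 days, and the rate to about 4.5 to 6%.

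**ICU stay.** Intervention description {11a} plans extubation within 12 h, after which stable patients move to the neurology floor, so survivors' ICU stays may be short. Assume a survivor mean of 1.5 to 2 days, with deaths in the ICU at a mean of 4 days. At 20% versus 10% deaths the gap is then 0.10 × (4 − 1.5) = +0.25 days or 0.10 × (4 − 2) = +0.2 days. The higher-mortality arm has the longer mean stay and is significantly shorter in only about 1% of trials. The direction for ICU stay therefore cannot be fixed from the article.

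**The case against.** The strongest reply is that the article is silent. It does not say that deaths are counted as short stays, it names no test for these outcomes, and such a rule often sits in a full protocol or analysis plan that is not shown. Time to discharge could also be read as calling for a time-to-event method. This stands in part: a reader might infer that the plan deliberately scores death as a short stay, and no section says so. But the article does state the recorded variable, the population and the basis for choosing the test. Together these lead to a comparison of plain durations in everyone randomised. A time-to-event method would not settle the matter by itself, because death would still have to be classed as an event, a censoring or a competing event.

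Other parts of the reply stand in full.

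- Excess deaths would not be hidden. Mortality is listed separately, and the primary outcome scores death as a failure.
- A reader might infer that an objective of faster recovery would be answered in the wrong direction. The Secondary objectives give stay no direction and do not call it a measure of recovery; the directional hypothesis concerns the mRS.
- A reader might extend the point to the prolonged ICU stay item (> 48 h). That item is a complication listed beside mortality, and scoring deaths as prolonged would count them twice. No change is asked for there.
- The size rests on assumed mortality differences. Nothing in the article supports a doubling of mortality.

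**Conclusion.** The point holds in a limited form. As written, nothing separates discharge alive from death, so an in-hospital death ends the recorded stay and more early deaths can shorten an arm's hospital stay.

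Under the assumed figures, the rate of a misleading significant result is about twice its equal-mortality level of about 2.5% when deaths differ by 5 points, and about 12% when they differ by 10 points. It is smaller if deaths occur nearer the usual time of discharge. For ICU stay the bias may run either way. A claim that both stays always favour the arm with more deaths is not supported.

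The primary outcome and the sample size are not touched. The point is minor to moderate and confined to secondary outcomes.

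**What to change.** Before the analysis, add one rule. Analyse time to discharge alive, from hospital and from ICU, with death as a competing event, and compare the cumulative incidence of live discharge. Alternatively, rank in-hospital deaths as the longest stay in the rank-sum test. Read the result alongside in-ICU and in-hospital mortality, and give stay among survivors descriptively only.

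The change is to analysis wording. Stays and mortality are already among the planned data. The cost is a summary slightly less familiar than median days for all patients.

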### Eligibility criteria {10}

#### Inclusion criteria

Adult (age ≥ 18 years), both genders.Acute ischemic stroke due to large intracranial vessel occlusion demonstrated on CT-angiography in the following anterior circulation locations (occlusion of the internal carotid artery and/or middle cerebral artery in segments M1, M2, M3) within 24 h of symptom onset.Patients admitted with a NIHSS neurological status ≥ 6.Patients who received endovascular treatment under general anesthesia and mechanical ventilation with satisfactory reperfusion (TICI 2b-2c-3).Patients intubated in the interventional radiology room.Patients admitted to the ICU with mechanical ventilation.Written informed consent from the patient or proxy (if present) before inclusion or once possible when patient has been included in a context of emergency.

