### Intervention description {11a}

In both groups of patients undergoing endovascular thrombectomy in the interventional radiology room, general anesthesia will be administered at the discretion of the attending anesthesiologist. All patients will be monitored with electrocardiogram, hear rate, pulse oxygen saturation, invasive blood pressure, end-tidal carbon dioxide, inspired oxygen fraction, and blood glucose. Plasma glucose will be maintained within the range of 140–180 mg/dL, and systolic blood pressure will be targeted to be kept between 140 and 180 mmHg, with vasopressor support if necessary. Following endovascular treatment, patients will be transferred to the ICU, and if they meet the inclusion criteria, they will be then randomized into one of two groups: early vs delayed extubation.

In the ICU, patients will be monitored similarly to the interventional radiology room. Because the trial includes patients who have undergone satisfactory endovascular thrombectomy (TICI 2b-3), systolic blood pressure will be targeted to be maintained between 120 and 140 mmHg, with vasopressor support if necessary. Patients allocated to the early extubation group will be extubated within 6 h after endovascular thrombectomy, while those in the delayed extubation group will be extubated between 6 and 12 h after treatment.

During both assigned time frames, patients will be extubated if they meet the following criteria:Hemodynamic stability: The patient should be hemodynamically stable, with blood pressure within acceptable ranges and no significant need for vasopressor support.Respiratory stability: The patient should have adequate respiratory function, with effective mechanical ventilation and no signs of acute respiratory distress.Neurological status: The patient should be awake, alert, and able to follow simple commands. Assessment of airway protection and swallowing capacity will be considered.Assessment of cough and secretion clearance: The patient should have the ability to cough and clear secretions effectively to prevent respiratory complications.Response to spontaneous ventilation: A spontaneous breathing trial may be conducted to assess the patient’s ability to breathe independently without ventilatory support.

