## Assignment of interventions: allocation

### Sequence generation {16a}, concealment mechanism {16b}, implementation {16c}

Randomization will be performed immediately after the patient is admitted to the ICU. Enrolled participants will be randomized in a 1:1 ratio for early or delayed extubation. To ensure balance between the two groups, a computer-generated random block number table will be used (blocks of 8). A designated staff member, not involved in extubation, anesthesia management, or follow-up will handle recruitment and generate the allocation randomization sequence. The staff member will implement the allocation sequence through opaque, sealed, and stapled envelopes.

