### Methods for additional analyses (e.g., subgroup analyses) {20b}

Primary outcome will be analyzed in following subgroups: age, gender, body mass index, NIHSS score at admission, ASPECTS, site of arterial occlusion, time from symptom onset to endovascular thrombectomy, use of intravenous thrombolysis.

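### Work-flow times that end before randomisation are listed as secondary outcomes, so no difference in them can be an effect of extubation timing

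*Protocol article*

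**What the plan says.** Under Secondary outcomes measures, the list that opens with "The secondary outcomes of this study will be as follows" closes with "Work-flow time, including stroke onset to door time, to artery puncture, and to reperfusion or procedure completion".

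The time of allocation is given in two sections. Intervention description {11a} says: "Following endovascular treatment, patients will be transferred to the ICU, and if they meet the inclusion criteria, they will be then randomized". The section on sequence generation, concealment and implementation {16a–16c} says: "Randomization will be performed immediately after the patient is admitted to the ICU". Table 1 agrees, with allocation in the column that follows treatment, and the inclusion criteria require that satisfactory reperfusion has already been obtained.

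The same times appear in two other roles. The data collection section records the clock times of onset, arrival, puncture and recanalization under baseline and intraoperative data. Methods for additional analyses {20b} lists "time from symptom onset to endovascular thrombectomy" as a subgroup factor for the primary outcome.

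On testing, Analysis of the secondary outcomes says of its analyses that "those whose *p*-value is lower than 0.05 will be considered statistically significant values". The baseline description section separately plans significance tests on baseline characteristics.

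**The concern.** An outcome of a randomised comparison must be able to respond to what was allocated. These intervals are fixed when the envelope is opened, so the effect of allocation on them is zero by design. Calling them outcomes gives an imbalance the appearance of a treatment effect. In a baseline table the same imbalance would be read correctly, as chance or as a prompt to look at how allocation was carried out.

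The label also conflicts with the article's own use of onset-to-thrombectomy time as a subgroup factor. That use requires the variable to be unaffected by treatment. It cannot be a pre-treatment factor in one analysis and a consequence of treatment in another.

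**Working it through.** **Step 1. Order of events.** This is what decides the point.

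| Event | Source | Position relative to allocation |
|---|---|---|
| Arrival at hospital (onset to door) | Secondary outcomes; baseline data list | Before |
| Artery puncture | Secondary outcomes; baseline data list | Before |
| Reperfusion or end of procedure | Secondary outcomes; inclusion criteria | Before; satisfactory reperfusion is an entry condition |
| ICU admission | Intervention description {11a} | Before, immediately preceding |
| Randomisation | Sections {11a} and {16a–16c}; Table 1 | – |
| Extubation | Intervention description {11a} | After |

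The last event that closes any named interval is the end of the procedure, and it precedes ICU admission. I read all three intervals as starting at stroke onset. If they were instead successive segments (door to puncture, puncture to reperfusion), they would still all end before allocation. The item is worded to allow further times, but none ending after randomisation is named.

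**Step 2. What a test would deliver.** The article gives no figure for this, so the following is a derived illustration. Inputs: the two-sided 5% level from the sample size section, the 0.05 threshold in the secondary analysis section, and three intervals from the outcome list. The null hypothesis is true for each.

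- One test: false-positive rate 0.05.
- At least one of three, lower end: 0.05, if the three tests always agree (complete dependence).
- At least one of three, upper end: 1 − (1 − 0.05)³ = 1 − 0.857375 = 0.142625, or 14.3%, if the tests are independent. For two-sided tests on jointly normal statistics, Šidák's inequality makes independence the worst case.

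Intervals that share onset as their origin are nested and positively correlated, so the truth should lie inside this range. A null simulation illustrates where. It used 4,000 runs, 174 patients, blocks of 8 and Wilcoxon rank-sum tests. Onset-to-door time was log-normal with log-scale mean 5 and SD 0.7, and two log-normal segments were added in turn (4 and 0.4; 3.7 and 0.5). The per-test rates were 5.4%, 5.3% and 5.1%, and at least one test was significant in 7.5% of runs. The simulation error on a 5% rate is √(0.05 × 0.95 / 4000) = 0.0034, so the per-test rates agree with 5%. The distributions are assumptions, so 7.5% is an example and not an estimate for this trial.

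**Step 3. What is not affected.** The sample size rests only on the primary outcome. With 55.5% and 33.9%, mean 44.7%, two-sided α = 0.05 and 80% power:

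n = [1.960 × √(2 × 0.447 × 0.553) + 0.842 × √(0.555 × 0.445 + 0.339 × 0.661)]² / (0.555 − 0.339)² = 82 per group after rounding up.

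Allowing for 5% losses, 82 / 0.95 = 86.3, so 87 per group and 174 in total. This matches the sample size section. Work-flow times do not enter the calculation.

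**The case against.** The strongest reply is that this is a labelling slip and that no test of these times is actually planned. The section on secondary analyses speaks of answering the secondary objectives, and the secondary objectives do not mention work-flow time. They do include finding factors linked to poorer functional status, so a descriptive or predictor role may be what was meant. This stands in part: between-arm testing is an inference, and the false-positive figures are therefore conditional. It does not remove the point, because the article calls these times secondary outcomes and nothing in it withdraws that.

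A reader might also infer three stronger things that the document does not support.

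- **A false-positive chance of 14% to 19%.** The upper figure, 1 − 0.95⁴ = 18.5%, needs reperfusion and procedure completion to be counted as two separate times and all four tests to be independent. The article offers those two as alternatives, and nested intervals are not independent. For three intervals, 14.3% is the ceiling.
- **That any difference must be chance.** This holds only if allocation is sound. Otherwise an imbalance in pre-randomisation times could signal selection. What can be said without that condition is that it is not an effect of extubation timing.
- **That these times are used as endpoints in place of adjustment.** The primary analysis section lets covariates enter on clinical judgment and statistical criteria, and the outcome list excludes none of them. The article says only that such times may influence outcome and gives no effect size, so they cannot be called strong prognostic factors on its evidence.

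It is also fair to say that the choice of covariates is commonly left to an analysis plan, which is not shown here. For that reason adjustment appears below only as an option.

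**Conclusion.** The point holds as a misclassification. All the named work-flow intervals end before randomisation, and the article itself gives the same times a baseline role elsewhere. No between-arm difference in them can be attributed to extubation timing. This follows from the stated order of events and needs no numerical assumption.

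The size is modest. If the times are tested at p < 0.05, the false-positive rate is about 5% per interval and 5% to 14.3% for at least one of three. This assumes that tests are run as for the other secondary outcomes, that allocation is sound, and that the correlation lies somewhere between complete dependence and independence. The harm is a possible misreading of a secondary result. The primary outcome definition and the 174-patient sample size are untouched.

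**What to change.** 1. Remove work-flow times from Secondary outcomes measures.
2. Report them by arm, descriptively, with the baseline and procedural data.
3. In the section describing the groups at baseline, exempt these times from the planned significance tests. Without this, moving the item would only move the same uninformative tests to another table.
4. Optional: name onset-to-reperfusion time in advance as an adjustment covariate for the primary outcome, instead of leaving its inclusion to univariate p-values and stepwise/AIC selection. This is an improvement in its own right, and the reclassification does not depend on it.

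The cost is a change of wording in two sections, or three with the option. No new data are needed, since the clock times are already collected. The article says that protocol amendments go to the ethics committee for approval, so the change would follow that route.
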